#### Primary Objective

The main objective of the POC study is to evaluate how women experience the chatbot-based version of the WHO-validated intervention SH+. It aims to assess the following areas: (1) the user experience (UX) and the usability of the virtual coach, ALBA, installed in the TreC research app environment and (2) how users felt during the intervention, using ALBA, as reported through semistructured interviews. The IT evaluation of the TreC research app itself will be presented in another study.

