#### Phase 4: Follow-Up

Four months after the conclusion of exposure to SH+ intervention, women who have given consent will be invited to participate in a semistructured interview to investigate their experience of using ALBA and the TreC research app to understand how the women felt during the intervention. In addition, the long-term effects of stress will be collected by administering a follow-up questionnaire.

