#### Secondary Outcomes

The variables expressing the psychological well-being outcomes will be assessed by administering self-report questionnaires at the beginning (screening and week 0) and at the end (week 6) of the intervention (Textbox 2 provides a detailed overview of the questionnaire adopted). The end points to be measured include the scores of individual questionnaire items, the average scores of the questionnaires, and the differences between the average scores of the questionnaires at 2 survey times. In addition, the Perceived Stress Scale (PSS) [38] will be administered during a follow-up conducted 4 months after the study’s conclusion.

Both the clinical and usability tests will yield within-subject and between-subject comparison results.

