#### Phase 1: Screening

To fulfill the verification of the inclusion criteria from 7 to 9 and the exclusion criteria 5 and 6, the researchers will administer the screening questionnaires through LimeSurvey (LimeSurvey GmbH; Textbox 2).

After processing the results of the screening questionnaires and the various sociodemographic inclusion criteria, the women will be contacted again, and the following scenarios will open.

First, the participant does not meet the inclusion criteria due to demonstrating a markedly positive state of psychological well-being, as indicated by a stress level <15.9 on the Kessler Psychological Distress Scale (K-10) [28], a general well-being score <3 on the General Health Questionnaire (GHQ) [39], and a general well-being score >80 on the “Mental Health” scale of the Short Form Health Survey 36 (SF-36) [29]. In such cases, the women will not be enrolled in the study, and the reasons for exclusion will be shared along with the screening questionnaire results, but upon the participant’s request.

Second, the participant does not meet the inclusion criteria due to exhibiting a markedly negative state of psychological well-being or signs of psychopathology, as indicated by a score <30 on mental health scale of the SF-36 and a K-10 score >29.9. In addition, in the second case, the participant will not be able to be enrolled in the study, and the reasons for exclusion from the study will be returned, and only upon request of the participant will the results obtained from the screening questionnaires be returned. Furthermore, indications of local services to contact for problems will be appropriately provided. This is to provide the participant with a structured and agreed system of referral to a qualified support service and taking charge where appropriate.

Third, the participant meets the inclusion criteria. In this case, the participant is enrolled in the study. The participant will also be asked if they would like to participate in a qualitative interview and in compiling a last questionnaire about stress 4 months after delivery. In case of positive feedback, the telephone number will be collected to facilitate contacts and follow-up interviews.

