PSS is a self-report questionnaire used to measure perceived stress. In particular, the objective is to determine the degree to which situations are perceived as stressful in a person’s daily life. Using 10 items rated on a 5-point Likert scale, this tool assesses participants’ thoughts and feelings over the past month regarding specific events, such as how often they felt unable to control important aspects of their lives. For each item, participants indicate the frequency on a scale from 0 (“never”) to 4 (“very often”).

SF-36 [29] is the most widely used general health measurement tool. It is a questionnaire divided into 8 sections: physical functioning (10 items), limitations due to physical health (4 items), limitations due to emotional problems (3 items), energy and fatigue (4 items), emotional well-being (5 items), social activities (2 items), pain (2 items), and perception of general health (36 items). For each dimension, the scores of the questions are coded, summed, and transformed into a scale ranging from 0 (worst health state) to 100 (best health state).

The platform adopted for the intervention allows for the recording of activity logs, enabling proper mapping of patients’ actions and experiences. This covers a range of logs, assessing whether the participant is properly exposed to the intervention protocol while recording use patterns (eg, session execution time, number of accesses, and use patterns of different features). Included among the variables considered are any missed sessions or interruptions. These data will be correlated with acceptability scores during the analysis phase. If a patient does not complete activities and fails to fill in specific questionnaires (leading to missing data), specific information on patients’ experiences and platform use will be collected during the scheduled postintervention interview sessions.

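### The 4-month PSS is bundled with the optional interview in one enrolment question, while other sections list it as a measure with no opt-in

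*Protocol article*

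**What the plan says.** Four places in the protocol article bear on who provides the 4-month PSS.

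- **Data Collection, Phase 1: Screening.** Women who meet the criteria are asked in a single question "if they would like to participate in a qualitative interview and in compiling a last questionnaire about stress 4 months after delivery". The text continues: "In case of positive feedback, the telephone number will be collected to facilitate contacts and follow-up interviews". Nothing is said about a woman who would accept one part and decline the other.
- **Design and Study Plan, Phase 4: Follow-Up.** Here "women who have given consent will be invited to participate in a semistructured interview to investigate their experience". A separate sentence, with no consent condition of its own, says that "the long-term effects of stress will be collected by administering a follow-up questionnaire".
- **Secondary Outcomes.** The PSS "will be administered during a follow-up conducted 4 months after the study’s conclusion", with no restriction.
- **Textbox 2.** The follow-up entry lists the PSS and the interview, again with no restriction. The PSS is the only questionnaire there.

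The interviews carry two further tasks. The Primary Objective includes "how users felt during the intervention, using ALBA, as reported through semistructured interviews". For women who leave activities and questionnaires incomplete, Psychological Assessment says that information on their experiences and "platform use will be collected during the scheduled postintervention interview sessions". The same paragraph describes activity logs that capture missed sessions and interruptions, with no opt-in stated.

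The Data Analysis overview plans multiple imputation where appropriate and intention-to-treat inclusion of dropouts wherever feasible.

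**The concern.** A 10-item scale and a recorded interview of about 20 minutes ask very different things of a participant. Offering them as one choice means that a woman who does not want the interview may never be offered the scale. The app already administers the study's questionnaires, so no technical reason for the bundling is evident.

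Three things are at stake:

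- **Who is measured.** The only quantitative evidence on durability could come from women who volunteered for an interview.
- **How many are measured.** The sample size allows for dropout but not for an opt-in.
- **What is learned about stopping.** Logs show that a woman stopped and when. Why she stopped is planned only through interviews that she must have agreed to. Retention and dropout rates are among the benchmarks for a larger trial (Results section), so the reasons matter.

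**Working it through.** **1. The plan's own figure.** The inputs from Sample Size are a mean difference of 1.00, SD 2.00, α = .025 and power 0.80. Then d = 1.00/2.00 = 0.50. A two-sided paired t test (noncentral t) gives n = 41 with power 0.805, so the stated 41 is reproduced. Recruiting 50 with 20% dropout leaves 50 × 0.80 = 40, with power 0.79. Opt-in loss enters nowhere.

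**2. The passages side by side.** The screening procedure makes the PSS part of the optional package. Secondary Outcomes and Textbox 2 do not. Phase 4 limits the interview and leaves the questionnaire's population open. The privacy section asks for specific consent to telephone contact for interviews and does not mention the PSS. The document therefore supports two readings: PSS from all enrolled women, or PSS only from those who agree to the package.

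**3. Illustrative loss of numbers under the second reading.** Uptake is not given; 40% to 100% is assumed. If dropout is independent of the opt-in, n = 50 × 0.80 × uptake. If dropouts come first from the women who declined, n = the smaller of 40 and 50 × uptake. Power is for d = 0.50 at two-sided α = .025.

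| Assumed uptake | n, independent | Power | d detectable with 80% power | n, dropouts among decliners | Power |
|---|---|---|---|---|---|
| 100% | 40 | 0.79 | 0.50 | 40 | 0.79 |
| 80% | 32 | 0.68 | 0.57 | 40 | 0.79 |
| 60% | 24 | 0.53 | 0.67 | 30 | 0.65 |
| 50% | 20 | 0.44 | 0.74 | 25 | 0.55 |
| 40% | 16 | 0.34 | 0.84 | 20 | 0.44 |

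**4. Illustrative shift in the mean.** The responder mean differs from the mean of all enrolled women by (share missing) × (gap between responders and non-responders). The gap is not in the document; 0.25, 0.5 and 1.0 SD are assumed.

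| Share with a 4-month PSS | Gap 0.25 SD | Gap 0.5 SD | Gap 1.0 SD |
|---|---|---|---|
| 80% (dropout only) | 0.05 | 0.10 | 0.20 |
| 64% (80% uptake) | 0.09 | 0.18 | 0.36 |
| 48% (60% uptake) | 0.13 | 0.26 | 0.52 |

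With a gap of 0.5 SD and 60% uptake, the opt-in adds 0.26 − 0.10 = 0.16 SD to the shift from dropout alone, against a planned effect of 0.50.

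**5. What imputation can do.** Multiple imputation from the week 0 and week 6 scores corrects the part of the selection that those scores explain. It cannot by itself remove selection that depends on month-4 stress that was never observed.

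**The case against.** The strongest reply is that the restriction on the PSS is inferred. Only the screening text joins the two requests, and no sentence says that a woman who declines the interview will not receive the scale. That stands. It makes this a conflict to be resolved, not a proven exclusion.

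Several stronger readings are tempting, and the documents do not support them:

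- **That information on dropout comes only from the interviews.** The logs record use, missed sessions and interruptions for everyone. Only the explanation depends on interviews.
- **That non-completers are left out.** The question is put at enrolment, before exposure, and does not depend on completion. The protocol means the interviews to cover women who did not complete. They may well be under-represented, but no rule excludes them. Because the choice precedes exposure, its link with later improvement may also be weak.
- **That the acceptability evidence as a whole is selected.** The four primary usability and user experience questionnaires at weeks 3 and 6 fall outside the opt-in, and the interviews supplement them. Only the interview part of the primary objective is exposed.
- **That the study promises power at month 4 and misses it.** The calculation gives the pre-post comparison as its example. No power is claimed for the 4-month PSS.

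The four-month delay before the interview is also open to question because of recall. A late interview does show longer-term use, so its timing is a trade-off and not an error.

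**Conclusion.** The point holds as an inconsistency with a practical consequence. The protocol does not settle whether the 4-month PSS is sought from all enrolled women or only from those who accept the interview package. If the screening procedure is followed as written, the only long-term questionnaire comes from a self-selected subset, and imputation may not repair this. Explanations of non-completion would then be missing for non-completers who did not opt in.

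The size cannot be fixed from the document. With 60% uptake, 24 to 30 women would remain under the two dropout patterns shown, with power of 0.53 to 0.65 at d = 0.50, compared with 0.79 for 40. With high uptake, or with dropout concentrated among decliners, little may be lost. The direction of any shift is likewise an assumption; a favourable one is plausible but not shown. The measure is secondary and the study is an uncontrolled proof of concept. The change is worth making mainly because it costs so little.

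**What to change.** Reconcile Phase 1: Screening, Phase 4: Follow-Up, Textbox 2 and Secondary Outcomes by separating the two requests:

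- Send the 10-item 4-month PSS through the app to every enrolled woman, including those who stopped the programme, under the main consent. She remains free not to answer.
- Keep only the interview and the telephone contact as an opt-in.
- Optionally, add one in-app question on the reason for stopping when a session or questionnaire is missed, so that explanations do not depend on the interview.

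The cost is a small change to the consent wording and one more in-app questionnaire. Women who no longer open the app may still not respond, so the change reduces selection without removing it.

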#### Phases 2 and 3: Enrollment and Participation

##### Overview

To properly assess included participants’ experience during the psychoeducational pathway, some questionnaires were adopted and delivered at the beginning (phase 2), during, and at the end of the interaction with ALBA (phase 3), as shown in Textbox 2.

Specifically, 5 questionnaires will be administered at the beginning (week 0) and at the end of the intervention (week 6) together with the initial screening questionnaires, which aim to investigate stress level, self-efficacy, emotional regulation, psychological flexibility, coping strategies, well-being, and level of psychological well-being. None of these questionnaires has diagnostic purposes. Therefore, they will not be used to diagnose psychopathology but only to collect descriptive data.

Four more questionnaires will be sent during the process to analyze the usability and involvement of the participant with the app and with the virtual coach, ALBA. Specifically, the usability and UX questionnaires will be administered at the end of week 3 (3 questionnaires) and week 6 (4 questionnaires).

A detailed description of each instrument that will be administered is presented in the subsequent sections.

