**Results:**

The app is expected to demonstrate high usability and engagement, aligning with the WHO Self-Help Plus protocol. Improvements in psychological well-being and quality of life are anticipated. Data from this pilot will be analyzed using both quantitative and qualitative methods, with a focus on assessing feasibility, acceptability, and perceived utility and usability in supporting women during BC treatment.

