#### Phase 1: Screening

The screening phase is carried out by psychologists, and subsequent included participants are given access to the TreC research app.

#### Phase 2: Enrollment at Week 0

At the beginning of the path, ALBA will administer 5 self-report questionnaires to establish the baseline level of the examined variables (preassessment questionnaires). The participant can choose the best day and time to interact with ALBA (first interaction with ALBA).

#### Phase 3: Intervention Delivery From Week 1 to Week 5

Specifically, there is 1 psychoeducational session per week, and the contents will be presented in different formats (text, images, audio, and video tracks). Moreover, ALBA provides users with instructions on how to carry out simple exercises and fill in a personal diary. The questionnaires will be further administered by ALBA at the end of the course (at week 6) to verify whether participants have perceived a change in terms of psychological well-being and quality of life. In total, 4 questionnaires will be administered to evaluate usability and UX (weeks 3 and 6).

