**Screening**
Kessler Psychological Distress Scale (K10)General Health Questionnaire (GHQ)Short Form Health Survey 36 (SF-36)

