**At the end of the study (week 6)**
GHQPSSMPFIGSEERQCOPE-NVI-25UES-SF (this will be administered the following day so as not to burden the participant during completion)SUS (this will be administered the following day so as not to burden the participant during completion)ITA BUS B (this will be administered the following day so as not to burden the participant during completion)User Mobile Application Rating Scale (uMARS; this will be administered the following day so as not to burden the participant during completion)

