**Follow-up (4 months after the conclusion)**
PSSQualitative interview

The end points to be measured include the scores of individual questionnaire items, the average scores of the questionnaires, and the differences between average scores of the questionnaires at various survey times. In addition, the participants’ experiences with the app and interactions with ALBA, as well as their use of the intervention, will be evaluated through semistructured interviews conducted 4 months after the study concludes. These interviews will collect qualitative data to supplement the primary outcome information.

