#### Quantitative Analysis

Statistical data processing will be conducted using the software R (version 4.0.0; R Foundation for Statistical Computing) [47], SPSS (IBM Corp) statistics [48], Stata (version 17) [49], and Jeffreys’s Amazing Statistics Program [50].

Categorical variables will be summarized using absolute frequencies and percentage distributions, while quantitative variables will be summarized using specific measures of central tendency and variability. Descriptive analyses will cover psychological variables (stress level, anxiety level, depression level, emotional regulation, psychological flexibility, coping strategies, well-being, and health status) as well as UX and usability variables. Relationships between variables will be analyzed primarily using ad hoc statistical tests, including the chi-square test, Fisher exact test, paired *t* test, Wilcoxon signed rank test, and sign test, depending on the assumptions met. These tests will help identify differences between the beginning and end of the course within the same study sample for the variables under investigation. In addition, univariate logistic or multinomial regression models will be presented. To account for potential confounding factors, multiple regression models will be proposed, adjusting the effects of explanatory variables on outcome variables for possible confounders. Statistical significance will be found for each analysis with a *P* value ≤.05*.* The McNemar test [51] and Cochran Q test [52] will also be used to evaluate paired qualitative data.

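### The protocol promises a week-6 change in quality of life, but Textbox 2 repeats only the GHQ from screening; no listed score gives a separate anxiety or depression level

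*Protocol article*

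**What the plan says.** Textbox 2 of the protocol article is the instrument-by-visit schedule. Extraction has run its entries together, but they are readable.

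- Screening: "Kessler Psychological Distress Scale (K10)General Health Questionnaire (GHQ)Short Form Health Survey 36 (SF-36").
- Week 6, psychological part and first usability form: "GHQPSSMPFIGSEERQCOPE-NVI-25UES-SF". The K-10 and SF-36 are not in this list.
- Four-month follow-up: "PSSQualitative interview", that is, the PSS and an interview.

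The text around the schedule says more. The Overview of Phases 2 and 3 (Data Collection) points to Textbox 2 and has five questionnaires given at week 0 "and at the end of the intervention (week 6) together with the initial screening questionnaires", without naming a subset. The Phase 3 paragraph of Design and Study Plan gives the purpose of the week-6 assessment: "to verify whether participants have perceived a change in terms of psychological well-being and quality of life". Secondary Outcomes places the well-being measures "at the beginning (screening and week 0) and at the end (week 6) of the intervention". The abstract states: "Improvements in psychological well-being and quality of life are anticipated". The Results section likewise expects better quality of life.

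Quantitative Analysis says the descriptive analyses will cover "psychological variables (stress level, anxiety level, depression level, emotional regulation, psychological flexibility, coping strategies, well-being, and health status"). It then says the tests will look for differences between the start and end of the course in the variables under investigation.

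**The concern.** The text tells the reader that change in quality of life will be assessed at week 6, and it can be read as repeating all three screening instruments then. The schedule repeats one of the three. Whoever configures the app from Textbox 2 will collect no SF-36 or K-10 after screening. A week-6 assessment that was never given cannot be recovered, and the multiple imputation mentioned under Data Analysis cannot supply a variable that was observed in nobody at that visit.

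The labels in Quantitative Analysis are a related problem. Anxiety level and depression level appear as variables in their own right, but the instrument descriptions offer no score for either. The Results section makes significant change in psychological variables one of the benchmarks for a larger trial. For a variable without a score, or without a post value, that benchmark is undefined. The gap also leaves room for a GHQ or PSS result to be reported under a name it does not carry.

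**Working it through.** No calculated figure of the protocol is at issue, and the sample size of 41 does not enter. The check is a cross-tabulation of instruments against time points, taken from Textbox 2.

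| Instrument | Screening | Week 0 | Week 6 | 4 months |
|---|---|---|---|---|
| K-10 | yes | – | – | – |
| SF-36 | yes | – | – | – |
| GHQ | yes | – | yes | – |
| PSS | – | yes | yes | yes |
| MPFI, GSE, ERQ, COPE-NVI-25 | – | yes | yes | – |

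**Screening instruments repeated at week 6:** 1 of 3 (GHQ). The K-10 and SF-36 have no post-intervention time point.

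**Psychological instruments with both a pre and a post value:** 6 (GHQ, PSS, MPFI, GSE, ERQ, COPE-NVI-25).

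**Quality of life and health status.** Psychological Assessment presents the SF-36 as the general health measure, with eight sections scored 0 to 100. No other instrument is described in such terms: the GHQ is described as monitoring psychological well-being, and the PSS as measuring perceived stress. I therefore assume that the SF-36 is what would carry quality of life and health status. Under Textbox 2 it yields a screening value and no change score.

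**Anxiety and depression.** I went through the instrument descriptions for a separate score. None is described. The GHQ-12 items are said to touch on symptoms of both, but the only score given is a total with a maximum of 36. The K-10 items touch on nervousness, sadness and hopelessness, again with one total (10 to 50). Of the eight variables in the Quantitative Analysis list, two therefore have no score of their own, and one (health status) has a screening value only.

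**Burden of adding the instruments.** The SF-36 has 36 items (taken from its name, since the section counts printed in the article do not add to 36) and the K-10 has 10: 36 + 10 = 46. The psychological set already scheduled at week 6 is GHQ-12 12 + PSS 10 + MPFI 12 × 5 = 60 + GSE 10 + ERQ 10 + COPE-NVI-25 25 = 127 items. Adding both gives 127 + 46 = 173, an increase of 46/127 = 36%. Adding the SF-36 alone gives 127 + 36 = 163, an increase of 36/127 = 28%.

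**The case against.** The sentence in the Overview of Phases 2 and 3 is loosely built. It defers to Textbox 2, and it may mean only that the screening scores add to the baseline. Secondary Outcomes supports this by counting screening as part of the beginning, and the GHQ has its pre value only there. The constructs listed in the same sentence do not include quality of life. This reading is fair, and it weakens the direct contradiction. It does not remove the gap: if the screening instruments are not repeated, the quality-of-life purpose stated for week 6 certainly has no instrument behind it.

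The list in Quantitative Analysis is introduced as descriptive, and health status can be described from the screening SF-36. That stands for the sentence itself, but the sentences that follow test start-to-end differences in the variables under investigation without excepting any.

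The consequences are also limited. The secondary objective and outcomes name psychological well-being, not quality of life. The abstract and Results state expectations, not endpoints. The K-10 is described as a screening tool, and nothing specifically promises a K-10 change. All of this stands and lowers the weight of the point.

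A reader might infer that anxiety and depression have no instrument at all. The documents do not support that: the GHQ-12 is described as covering both kinds of symptom and is given at screening and week 6, and individual item scores are listed among the endpoints. What is missing is a separate level for each.

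**Conclusion.** The point holds as an inconsistency that should be corrected. The stated purpose of the week-6 assessment includes quality of life, and the schedule gives no general health instrument after screening. If Textbox 2 governs, no pre-post change can be computed for 2 of the 3 screening instruments. This rests on two assumptions: that the app follows Textbox 2, and that the SF-36 is the intended carrier of quality of life and health status.

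A reader might go further and conclude that quality-of-life change cannot be measured in this study. That does not follow unconditionally. If the text of Phases 2 and 3 governs and all three screening instruments are repeated, the values will exist and only Textbox 2 is wrong.

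Nor is distress left without a pre-post measure: the GHQ covers general distress and the PSS covers stress. Only distress on the K-10 is lost. The primary outcomes of user experience and usability and the six instruments with both values are unaffected, so this does not threaten the main purpose of the study.

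**What to change.** Make the Phase 3 paragraph, the Overview of Phases 2 and 3 and Textbox 2 agree, by one of two routes.

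1. Add the SF-36 to the week-6 list, and the K-10 if its repetition is intended, and state that the screening score is the pre value, as is already the case for the GHQ. The cost is 36 to 46 items per woman at week 6. The four usability forms are already moved to the following day, so the burden can be spread. Giving both instruments at week 0 as well would bring the addition to 2 × 46 = 92 items and is not needed to resolve this point.
2. Leave Textbox 2 as it is. Reword the Overview to say that only the GHQ is repeated from screening, and remove the claims of change in quality of life and health status from the abstract, the Phase 3 paragraph, Quantitative Analysis and Results. Health status can stay as a screening descriptor. This costs only an edit.

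Route 1 helps only women who have not yet passed week 6. If some have, report the SF-36 change with that limit, or take route 2.

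Under either route, delete anxiety level and depression level from Quantitative Analysis, or replace them with the GHQ-12 total, named as general distress. This costs nothing.
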